### Blinding

It is not possible to blind study patients as RO THA is associated with an additional incision over the iliac crest for insertion of the acetabular registration pins. However, all observers recording radiological outcomes will remain blinded to the treatment group. Study patients will be identifiable with a unique study number. Only the research physiotherapist will have the key to identify individual patients and their respective treatment arm. Any documents related to the study will be archived directly at the study site by the research physiotherapist within a locked filing cabinet in a locked research office. This office has swipe card access with on-site security and 24-h CCTV surveillance. Patient data will be logged electronically using each patient’s unique identification number with computer software on an encrypted, password-protected research computer.

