The main limitations of existing studies comparing CO THA versus RO THA are that they are based on cadaveric specimens or retrospective clinical trials with limited data on functional outcomes, radiological results, or complications [6, 7, 9, 14, 15, 20]. Within each treatment group, different preoperative imaging modalities were used for surgical planning, operative procedures were performed with varying implant designs, and postoperative rehabilitation was not standardised. Observers recording outcomes were not blinded to the treatment group, and follow-up of outcomes and complications within each treatment group was limited to the early postoperative period [6, 7, 9, 14, 15, 20]. There is a need for high-quality evidence comparing CO THA versus RO THA. It is possible to improve on these previous studies by using the same preoperative planning technique in both treatment groups, prospectively randomising study patients to the treatment groups, and collecting data on a more comprehensive and robust range of clinical, functional, and radiological outcomes. All operative procedures will be undertaken using the standard posterior approach, sitting and standing spinopelvic radiographs will be used to assess patient-specific functional pelvic kinematics, and identical implant designs will be used in both treatment groups, which will help to blind observers recording radiological outcomes. The findings of this study will enable an improved understanding of differences in CO THA versus RO THA with respect to patient satisfaction, functional outcomes, implant survivorship, cost-effectiveness, and complications.

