### Outcomes

All study patients will undergo review by two observers (one orthopaedic registrar and one clinical research fellow) at 6 weeks, 6 months, 1 year, and 2 years following surgery. During these follow-up times, predefined clinical, functional, and radiological outcomes will be recorded by these observers using case report forms (CRFs). The following outcomes will be recorded in all study patients:
Accuracy of achieving the planned implant positioning and hip biomechanics (horizontal centre of rotation, vertical centre of rotation, acetabular offset, femoral offset, and leg-length discrepancy) as assessed using CT scanograms performed postoperatively at 6 weeksOperating time (minutes)Time to hospital discharge (hours)Analgesia requirements during inpatient admission and postoperatively at 6 weeks, 6 months, 1 year, and 2 yearsPatient-reported outcome measures including Oxford hip score (OHS), Harris hip score (HSS), Hip disability and osteoarthritis outcome score (HOOS), University College Hospital hip (UCH) score, Western Ontario and Mcmaster Universities Osteoarthritis Index (WOMAC), and University of California at Los Angeles hip (UCLA) score preoperatively and postoperatively at 6 weeks, 6 months, 1 year, and 2 years following surgeryHealth-related quality of life as measured using European Quality of Life questionnaire with 5 dimensions for adults (EQ-5D) preoperatively and postoperatively at 6 weeks, 6 months, 1 year, and 2 yearsMobilisation distance (metres) and use of mobility aids during inpatient admission and postoperatively at 6 weeks, 6 months, 1 year, and 2 yearsRange of movement (degrees) in the hip joint in the supine position as assessed with a goniometer during inpatient admission and postoperatively at 6 weeks, 6 months, 1 year, and 2 yearsResource use and cost-effectiveness including comparisons between the two treatment groups relating to operating time, theatre efficiency, equipment and sterilisation costs, analgesia requirements, inpatient rehabilitation, time to discharge, outpatient follow-up, additional imaging costs, and need for further surgeryComplications

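### Assessor blinding is promised only for radiological outcomes, while the same two observers examine the patients and measure range of movement with nothing to hide the iliac crest incision

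*Protocol article*

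**What the plan says.** All references are to the protocol article.

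- **Blinding.** Patients are unblinded: "It is not possible to blind study patients as RO THA is associated with an additional incision over the iliac crest". The next sentence sets the scope for assessors: "However, all observers recording radiological outcomes will remain blinded to the treatment group". On custody of the allocation: "Only the research physiotherapist will have the key to identify individual patients and their respective treatment arm".
- **Statistical analysis.** The analyst is also blinded.
- **Outcomes.** A registrar and a research fellow review all patients at 6 weeks, 6 months, 1 year and 2 years. Of these two it says that "predefined clinical, functional, and radiological outcomes will be recorded by these observers using case report forms (CRFs". The listed outcomes include hip range of movement, by goniometer with the patient supine, during the inpatient stay and at each of those visits. They also include the 6-week CT scanogram measurements, which carry the primary comparison.
- **Objectives.** Range of motion is a named secondary objective.
- **Background.** Among the limitations of earlier studies: "Observers recording outcomes were not blinded to the treatment group". On blinding, the article's own claim is narrower: "identical implant designs will be used in both treatment groups, which will help to blind observers recording radiological outcomes".

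**The concern.** A goniometer angle depends on the judgement of the person reading it. If that person knows the arm and expects one technique to do better, the readings can shift systematically. A larger sample does not shrink such a shift, and a blinded analyst cannot remove it from data already recorded.

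The article treats the incision as enough to tell a patient which operation was done. An examiner working at the hip of a supine patient may see the same incision, and the inpatient measurement comes when it is most recent. No covering, and no instruction to patients about disclosure, is described.

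The second stake is the primary endpoint. If the two visit observers also record the CT results, the promise that radiological observers stay blinded depends on their not learning the arm while examining the same patients.

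**Working it through.** **1. Setting the sections side by side**

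| Question | Blinding | Outcomes |
|---|---|---|
| Who is kept blinded? | Observers recording radiological outcomes | Not stated |
| Who records radiological outcomes? | Not named | The registrar and the research fellow |
| Who records clinical and functional outcomes? | Not stated | The same two people |
| What reveals the arm? | The iliac crest incision | Not mentioned, although the same observers review every patient |

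Two readings are possible.

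- *The visit observers are the radiological observers.* They are then meant to be blinded, but they see the patients and nothing hides the incision. The promise is unsecured for range of movement and for the 6-week CT measurements.
- *Someone else reads the CT.* The radiological promise can then hold, but the Outcomes section is wrong about who records what, and the clinical measurements have no stated blinding.

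On either reading, range of movement is unprotected and the two sections need reconciling.

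**2. The plan's own figure**

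The only design figure is the sample size, and this point does not depend on it. Inputs from the Sample size section: means 3.7 and 2.9 mm, SD 1.0 mm, so effect size (3.7 − 2.9)/1.0 = 0.8; two-sided 5%; power 80%. The normal approximation gives 25 per arm. The exact two-sample t test gives 25.5, rounded up to 26 per arm, or 52 in all, with power 80.7%. Allowing for 10% attrition, 52/0.9 = 57.8, or 58; the plan sets 60. The stated figures reproduce.

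**3. Illustration of the bias (assumed inputs)**

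The article gives no SD for range of movement and no size of observer bias. Assume no true difference and a systematic reading shift of b standard deviations between arms. The two-sided 5% t test then follows a noncentral t distribution with 2n − 2 degrees of freedom and noncentrality b√(n/2), where n is the number per arm.

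- n = 30 (full recruitment): √15 = 3.873
- n = 26 (the size before the attrition allowance): √13 = 3.606

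| Assumed b (SD) | Noncentrality, n = 30 | False-positive rate, n = 30 | Noncentrality, n = 26 | False-positive rate, n = 26 |
|---|---|---|---|---|
| 0 | 0 | 5.0% | 0 | 5.0% |
| 0.1 | 0.387 | 6.7% | 0.361 | 6.4% |
| 0.2 | 0.775 | 11.9% | 0.721 | 10.9% |
| 0.3 | 1.162 | 20.8% | 1.082 | 18.6% |
| 0.5 | 1.936 | 47.8% | 1.803 | 42.4% |

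These rates are per comparison. They show how sensitive the test is to a shift, not how large the shift will be.

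**The case against.** The strongest reply is that the article never says the clinical observers know the arm. Only the research physiotherapist holds the key, and because the same two people record radiological outcomes, the Blinding section nominally covers them. This stands as far as it goes: it is not established that range of movement will be measured by unblinded observers. But custody of the key does not hide a wound, so the risk remains as an inference from the article's own account of the incision.

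Four further readings are tempting, and the article does not support them.

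- *Blinding stops at the radiological readers.* It does not; the analyst is blinded as well.
- *The incision is the stated reason for leaving observers unblinded.* It is given as the reason for not blinding patients. No reason is given about observers.
- *The trial claims to have fixed this very limitation.* It criticises unblinded observers in earlier work, but its own blinding claim concerns radiological observers only.
- *Covering the scar would solve the problem.* Patients know their arm and can disclose it, and patient-reported scores stay unblinded whatever is covered.

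It can also be said that masking in the examination room is operational detail which an article may leave to the full protocol. That is fair for the method of masking. It is weaker for its scope, which the article limits to radiological outcomes in both Background and Blinding.

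Finally, the bias sizes are assumed, and range of movement is one of ten secondary objectives. Both are true and limit the weight of the point.

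**Conclusion.** The point holds in a limited form and is worth acting on. Assessor blinding is promised for radiological outcomes only. Range of movement, a secondary objective, is measured by observers who see the patients with no stated protection, and this leaves it open to the weakness that the article criticises in earlier studies. The radiological promise is itself unsecured if those same observers record the CT results.

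The size of any bias is unknown. Across an assumed shift of 0.1 to 0.5 SD, the false-positive rate runs from about 7% to 48% at 30 per arm, and from about 6% to 42% at 26 per arm. The conclusion rests on two inferences: that the incision can be seen during the examination, and that nothing in the unseen full protocol already covers it. It does not show that observers are told the allocation or that the primary result is biased.

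**What to change.** Extend the Blinding section so that observers measuring range of movement are also kept blinded as far as possible:

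- At the inpatient measurement and at every follow-up visit, patients in both arms have both iliac crests covered before the observer enters, and are asked not to disclose their operation.
- Observers are not given the allocation or the operation note.
- At each measurement the observer records a guess of the arm on the CRF.

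Reconcile Outcomes and Blinding by stating who records which outcome, and have CT images read under study number only. Report patient-reported scores as unblinded.

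The cost is a covering per visit and one CRF field. Sample size, power, significance level and visit schedule do not change. Masking will sometimes fail, and the recorded guess will show how often. Keeping the observers out of theatre altogether would go further, but a registrar and a research fellow are also among the clinical team named under Recruitment, so that step might need other assessors and is not part of this proposal.

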### Sample size

Prior to commencement of this study, a pilot study was performed to assess the accuracy of restoring the centre of rotation using CO THA versus RO THA [15]. Using data from this study, the mean centre of rotation was set at 3.7 mm for CO THA and 2.9 mm for RO THA, with standard deviation of 1.0 mm. Using a two-tailed, two sample *t* test with a power of 80% (1–*β*), significance level of 5%, and an effect size of 0.8, this study required 52 patients (26 in each treatment arm) to detect the minimum difference between the two treatment groups. To account for 10% attrition in the sample size during follow-up, the total sample size was set at 60 patients.

### Statistical analysis

The analysis of the per-protocol population will be considered the primary analysis. The differences between the CO THA and RO THA groups will be analysed by calculating the difference from baseline, per patient, and a two-sided confidence interval for the difference between the changes from baseline values will be calculated. This confidence interval will cover the true difference in the percentage change from baseline with a probability of 95%. The following statistical methods will be employed to analyse the data: descriptive statistics, independent *t* test, paired *t* test, analysis of variance, Fisher exact test, chi-square test, and graphical displays. Assumptions of normality will be tested with the D’Agostino test. Assumptions of homogeneity of variance will be tested with Levene’s test. If the distributional assumptions are (severely) violated, non-parametric techniques, such as Mann-Whitney’s test will be employed. In the event that RO THA is converted to CO THA intraoperatively, analysis will be performed using the intention-to-treat population and the treatment actually received by the patients. Intraoperative conversion from RO THA to CO THA will be documented and presented and published as part of the study. All statistical analysis will be undertaken by a blinded observer. Statistical significance is set at a *p* value < 0.05 for all analyses, and all statistical analysis will be performed using SPSS software version 25 (SPSS Inc., Chicago, IL, USA).

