**Methods and analysis:**

This prospective randomised controlled trial will include 60 patients with symptomatic hip osteoarthritis undergoing primary THA. Following informed consent, patients will be randomised to CO THA (control group) or RO THA (investigation group) at a ratio of 1:1 using an online random number generator. Observers will review patients at regular intervals for 2 years after surgery to record predefined study outcomes relating to the accuracy of implant positioning, hip biomechanics, postoperative rehabilitation, clinical progress, functional outcomes, cost-effectiveness, and complications. Primary and secondary objectives will be used to quantify and draw inferences on differences in the efficacy of treatment between the two groups. Intention-to-treat and per-protocol population analysis will be undertaken. Intention to treat relates to the allocated treatment (CO THA or RO THA), and per-protocol refers to the actual treatment received by the patient. The following statistical methods will be employed to analyse the data: descriptive statistics, independent *t* test, paired *t* test, analysis of variance, Fisher exact test, chi-square test, and graphical displays. Ethical approval was obtained from the London-Bromley Research Ethics Committee, UK. The study is sponsored by University College London, UK.

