## Methods/design

### Objectives

The primary objective of this study is to compare the accuracy of achieving the planned centre of hip rotation in CO THA versus RO THA. This will be assessed within each treatment group by measuring the difference in the achieved centre of rotation on postoperative CT scanogram compared to the planned centre of rotation on preoperative pelvic CT scan. The study hypothesis is that RO THA will improve the accuracy of achieving the planned centre of rotation compared to CO THA.

The secondary objectives are to compare the following outcomes between the two treatment groups:
Accuracy of achieving planned component positioningAccuracy of restoring planned hip biomechanicsSpinopelvic functional kinematicsSurgical efficiencyPostoperative functional rehabilitationFunctional outcomesQuality of lifeRange of motionResource use and cost-effectivenessComplications

Specific study outcomes related to the primary and secondary objectives are discussed in the “Outcomes” section below.

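### The primary analysis of a superiority trial groups patients by treatment received, so a converted robotic case would count as a control in the decisive comparison

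*Protocol article*

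**What the plan says.** The Objectives section states a one-directional aim: "The study hypothesis is that RO THA will improve the accuracy of achieving the planned centre of rotation compared to CO THA". The Statistical analysis section then fixes the deciding population: "The analysis of the per-protocol population will be considered the primary analysis".

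The article defines that population in one place only, the Methods and analysis part of the Abstract: "per-protocol refers to the actual treatment received by the patient". The same paragraph ties intention to treat (ITT) to the allocated arm and promises both: "Intention-to-treat and per-protocol population analysis will be undertaken".

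One kind of crossover is addressed, in the Statistical analysis section: "In the event that RO THA is converted to CO THA intraoperatively", then "analysis will be performed using the intention-to-treat population and the treatment actually received by the patients". Such conversions are also to be documented and published. The sentence does not say which of the two analyses decides.

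**The concern.** Patients are randomised after consent, about two weeks before the operation. The treatment they actually receive is settled later, in theatre. Grouping by treatment received therefore lets an event after randomisation decide who is compared with whom, and in a superiority trial that is the comparison that should be protected.

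The foreseen movement runs one way. The Surgical intervention section describes registration and verification of bony landmarks for RO THA only. It is a reasonable inference, though the article does not say so, that a case abandoned at that step may also be harder to position accurately. Under the stated rule that case is removed from the robotic arm and added to the control arm, so both shifts favour the robot. Blinded radiological reading and a blinded analyst do not correct this, because the problem lies in the grouping and not in the measurement.

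At stake is whether a positive primary result reflects the device or partly reflects which patients remained in its arm.

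**Working it through.** **1. The plan's own figure.** Inputs from the Sample size section: means 3.7 mm (CO) and 2.9 mm (RO), SD 1.0 mm, two-sided 5%, power 80%. The difference is 3.7 − 2.9 = 0.8 mm, a standardised effect of 0.8. The exact two-sample *t* calculation gives 25.52, so 26 per arm and 52 in total, as stated. Allowing for 10% attrition, 52 / 0.9 = 57.8, so 58; the plan takes 60. Power is 86% at 30 per arm and 82% at 27 per arm (30 less 10%).

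**2. How far the two groupings differ under the planning means.** Let *k* of 30 robotic cases convert, with mean error *m* among them, and let unconverted robotic cases keep a mean of 2.9 mm.

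- ITT difference = 0.8 − *k*(*m* − 2.9)/30
- As-treated difference = 0.8 + *k*(*m* − 3.7)/(30 + *k*)

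For *k* = 3:

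- *m* = 3.7 (like an average manual case): ITT 0.8 − 3(0.8)/30 = 0.72 mm; as-treated 0.80 mm.
- *m* = 4.7: ITT 0.8 − 3(1.8)/30 = 0.62 mm; as-treated 0.8 + 3(1.0)/33 = 0.89 mm.
- *m* = 2.9: ITT 0.80 mm; as-treated 0.8 − 3(0.8)/33 = 0.73 mm.

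The two agree when *m* is about 3.3 mm. Above that, as-treated is more favourable to the robot than ITT; below it, less.

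**3. False effect when there is no true difference.** The article gives no conversion rate and no reason for conversion, so everything here is assumed: 30 per arm, SD 1.0 mm, the same mean in both arms, and the *k* most difficult robotic cases convert, with correlation ρ between difficulty and positional error. Let *S* be the sum of the *k* largest expected values in a standard normal sample of 30 (2.043, 1.616, 1.365, 1.179, 1.026).

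- As-treated bias = ρ × *S* × [1/(30 − *k*) + 1/(30 + *k*)]
- Bias if converted cases were excluded = ρ × *S* / (30 − *k*)

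For *k* = 3, *S* = 5.02 and the bracket is 1/27 + 1/33 = 0.0673. The bias is 0.10, 0.17 and 0.27 mm at ρ = 0.3, 0.5 and 0.8. Simulation (20,000 trials per scenario, two-sided *t* test at 5%) agrees and adds rejection rates:

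| Conversions of 30 | ρ | As-treated bias (mm) | Rejection |
|---|---|---|---|
| 0 | any | 0 | 5% |
| 1–5 | 0 (unrelated to difficulty) | 0 | 5% |
| 1–3 | 0.3 | 0.04–0.10 | 5–7% |
| 3 | 0.5–0.8 | 0.17–0.27 | 10–17% |
| 5 | 0.5–0.8 | 0.25–0.40 | 15–32% |

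ITT rejects about 5% of the time throughout. Excluding converted cases gives roughly half the bias: for *k* = 3 and ρ = 0.5–0.8, 0.09–0.15 mm and 7–9% rejection.

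**The case against.** **The bias is conditional.** With no conversions, the as-treated and ITT groupings coincide on this point. If conversion is unrelated to difficulty, for example because of a device fault, as-treated has no bias under the null and recovers the full 0.80 mm under the alternative, while ITT is diluted. This stands. Towards the robot is the expected direction, not a certain one.

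**ITT is already specified and conversions will be published.** This stands too. A reader might infer that the randomised comparison is lost, or that a positive result could never be told apart from selection. The documents do not support that, because the ITT result and the conversions would be reported beside the primary result. What remains is that the ITT result is not the one that decides.

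**The conversion sentence is not a contradiction.** A reader might take it as one. Under the Abstract's definition, treatment received is the per-protocol analysis, so the sentence only says that both planned analyses will be run. Its weakness is that it does not rank them.

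**Moving converted cases into the control arm rests on one Abstract sentence.** The Methods do not define the per-protocol population, and the full protocol is not shown. Under the more usual meaning, with converted cases excluded, the bias is about halved but does not disappear, so the recommendation is the same.

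**Conclusion.** The point holds as a choice that should be changed. The article states a superiority aim, makes per-protocol primary and defines that by treatment received. The deciding comparison therefore departs from the randomised groups whenever a robotic case is converted.

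The size cannot be fixed from the document. Against a planned difference of 0.8 mm, the false advantage ranges from 0 mm to about a third of that difference with 3 conversions and a strong link to difficulty (0.27 / 0.8 = 34%). It reaches about half with 5 (0.40 / 0.8 = 50%). The upper figures need both several conversions and a marked link, and neither is documented. This is a should-fix matter rather than a fatal flaw: the harm depends on an unknown number of conversions, and the planned ITT analysis would reveal it.

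**What to change.** In the Statistical analysis section, make the as-allocated comparison primary: all randomised patients with a 6-week CT scanogram, with converted cases kept in the RO arm. Keep the treatment-received analysis, labelled as supportive. Amend the conversion sentence to say that the ITT result decides.

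The text cost is one or two sentences, since ITT is already planned. The statistical cost is some power. If converted cases behave like average manual cases, the ITT difference is 0.8 × (1 − *k*/30), that is 0.80, 0.77, 0.75 and 0.72 mm for 0, 1, 2 and 3 conversions. Power is then 86%, 84%, 81% and 78% at 30 per arm, or 82%, 80%, 77% and 74% at 27 per arm with the same conversion rates. The planned 60 patients therefore tolerate about 2 conversions in 30 with complete data, or about 1 in 30 after 10% attrition, before power falls clearly below 80%.

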### End of protocol treatment

Reasons for going off study protocol include:
Completion of last follow-up visit 2 years after surgeryPatient non-compliance or withdrawal (the reason for discontinuation will be recorded in the case report form)Intercurrent death

All patients included into this study are free to withdraw from the study at any time without compromise to their future treatment. On withdrawal, patients will revert to the standard follow-up regimen for routine (non-study) THA at the study site. The end of study form will be completed and the reason for withdrawal documented. This form will also be completed if the patient is lost to follow-up or dies during the course of the study. Data to the point of discontinuation will be used for analysis.

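### Secondary hip scores and EQ-5D are compared by change from baseline (absolute or percentage, the text says both) without baseline adjustment, which costs precision

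*Protocol article*

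**What the plan says.** The Statistical analysis section of the protocol article sets the between-group method: "The differences between the CO THA and RO THA groups will be analysed by calculating the difference from baseline, per patient". The same sentence then names what is to be estimated from those values: "a two-sided confidence interval for the difference between the changes from baseline values will be calculated". The sentence after that describes the interval differently: "This confidence interval will cover the true difference in the percentage change from baseline with a probability of 95" per cent.

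The methods named are "descriptive statistics, independent *t* test, paired *t* test, analysis of variance, Fisher exact test, chi-square test, and graphical displays", with Mann-Whitney's test as the fallback if distributional assumptions fail badly. None of these, as named, includes the baseline value as a covariate.

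The Outcomes section lists six hip scores (Oxford, Harris, HOOS, UCH, WOMAC, UCLA) and EQ-5D, each recorded before surgery and at 6 weeks, 6 months, 1 year and 2 years.

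The primary outcome is different in kind. Under Objectives it is obtained by "measuring the difference in the achieved centre of rotation on postoperative CT scanogram compared to the planned centre of rotation". It is a deviation from a plan and has no preoperative value of its own.

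**The concern.** Subtracting the baseline amounts to assuming that follow-up scores rise one for one with baseline scores. When the true slope is smaller, the subtraction adds baseline noise to the comparison. It also over-corrects any chance difference between the arms at baseline. ANCOVA estimates the slope from the data instead.

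The trial has about 30 patients per arm, and its size was set for a radiological outcome, so precision on patient-reported outcomes is scarce. The Background attributes slow uptake of the robotic technique partly to limited evidence of functional benefit, so readers will look closely at these secondary comparisons. Wider intervals than the data require make them harder to interpret.

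The absolute and percentage wordings are a separate, plain inconsistency about the same interval. They define different estimates.

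**Working it through.** **1. The plan's own figure.** The Sample size section states that "the mean centre of rotation was set at 3.7 mm for CO THA and 2.9 mm for RO THA, with standard deviation of 1.0 mm", and uses a "two-tailed, two sample *t* test with a power of 80% (1–*β*), significance level of 5%, and an effect size of 0.8". The standardised difference is (3.7 − 2.9)/1.0 = 0.8. The normal approximation gives 25 per arm. The exact t calculation gives 25.5, so 26 per arm, with power 80.7%. Inflating for attrition, 52/0.9 = 57.8, so 58; the plan's 60 is close. The figure reproduces. It rests only on the primary outcome, so nothing below changes it.

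**2. Direction of the loss.** Let s0 and s1 be the standard deviations (SDs) before and after surgery, and r their correlation. Per patient:

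- change score variance: s0² + s1² − 2·r·s0·s1
- ANCOVA variance: s1²·(1 − r²)
- difference: s0² − 2·r·s0·s1 + r²·s1² = (s0 − r·s1)²

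A square is never negative. So, apart from the cost of estimating the slope, ANCOVA cannot be less precise, whatever r is. The two tie only when r = s0/s1.

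**3. Size of the loss.** This needs two assumptions that are not in the documents: s0 = s1, and a value for r. With equal SDs the ratio is (1 − r²)/[2(1 − r)] = (1 + r)/2. The evaluable number is taken as 60 × 0.9 = 54, or 27 per arm. Differences are in SD units of the score.

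| | r = 0.3 | r = 0.5 | r = 0.7 |
|---|---|---|---|
| Change variance (SD² = 1) | 1.40 | 1.00 | 0.60 |
| ANCOVA variance | 0.91 | 0.75 | 0.51 |
| Ratio | 0.65 | 0.75 | 0.85 |
| Interval narrower by 1 − √ratio | 19% | 13% | 8% |
| Simulated ratio, slope estimated (10,000 runs) | 0.67 | 0.76 | 0.87 |
| Power for 0.5 SD, change vs ANCOVA | 33% vs 47% | 44% vs 55% | 64% vs 71% |
| Difference detectable with 80% power, change vs ANCOVA | 0.92 vs 0.74 | 0.78 vs 0.67 | 0.60 vs 0.56 |
| ANCOVA patients worth 54 change-score patients | 35 | 41 | 46 |

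The last three rows use the formula variances. The simulated ratios show that estimating the slope costs about 2% of variance at this size. Using them, the intervals are about 18%, 13% and 7% narrower.

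Change is less precise than ignoring baseline altogether when its variance exceeds s1², that is when r < s0/(2·s1), or r < 0.5 with equal SDs. At r = 0.3 its variance is 1.40 times that of the follow-up score alone.

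**4. Chance imbalance.** With 30 per arm, the baseline difference D between arms has standard error √(2/30) = 0.26 SD, so an imbalance beyond 0.25 SD in either direction occurs in about one trial in three. With equal SDs, a given D shifts the change-score estimate by (r − 1)·D. At D = 0.25 SD the size of the shift is 0.7 × 0.25 = 0.18 SD at r = 0.3, and 0.3 × 0.25 = 0.08 SD at r = 0.7. ANCOVA removes it, given a linear relation.

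**The case against.** The strongest reply is that nothing here is invalid. Under randomisation the unadjusted change comparison is unbiased, the outcomes are secondary, and no power was claimed for them. A statistical analysis plan, not shown, might specify adjustment. All of this is fair and limits the weight of the point. It does not remove it, because the article states the change-score method outright and does not leave the choice open.

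The quoted sentence also names no outcome. The link to the hip scores and EQ-5D comes from the Outcomes section, which lists these as having preoperative values. The inference is reasonable, but it is an inference.

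Three stronger readings are tempting and not supported:

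- A reader might infer that the primary comparison or the sample size is weakened. It is not, because the primary outcome has no baseline value.
- A reader might infer that the scores will be analysed by separate t tests at each visit, discarding what dropouts contributed. The text does not say how the four visits are handled, and analysis of variance is among the listed methods. The End of protocol treatment section says "Data to the point of discontinuation will be used for analysis". Even separate tests would use every visit a patient attended; they would only fail to borrow it for later visits.
- A reader might take the low-correlation figures as the expected gain. The documents give no correlation. At r = 0.7 the gain is modest, and unequal SDs can move it either way.

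Finally, a mixed model for each of seven instruments in a trial of this size brings choices of its own, such as a covariance structure. That objection stands. Single-visit ANCOVA already delivers all of the gain calculated here.

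**Conclusion.** The point holds as a loss of efficiency in secondary outcomes, together with a wording conflict that must be resolved. That ANCOVA is at least as precise, apart from about 2% of variance for the slope, follows from the algebra without any assumed correlation. The size does depend on assumptions: with equal SDs and r from 0.3 to 0.7, the change score loses 35% down to 15% of the information, and ANCOVA intervals are about 19% down to 8% narrower before the slope cost.

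These figures apply to absolute change. If percentage change is meant, the (1 + r)/2 formula does not apply. That wording does not introduce a baseline covariate either, so the conflict needs settling on any reading.

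**What to change.** In the Statistical analysis section, for each outcome with a preoperative value (the six hip scores and EQ-5D), replace the change-score comparison with ANCOVA: postoperative score as outcome, arm and preoperative score as covariates. Report the adjusted mean difference and its 95% confidence interval at each visit. Delete the percentage-change sentence so that one scale is defined. Apply the planned distributional checks to the model residuals.

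As an optional extension, a repeated-measures mixed model with the same baseline covariate would also use the earlier visits of patients who drop out.

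The cost is wording, best settled before any unblinded analysis. No new data, visits or patients are needed. The price in precision is one estimated slope per model, about 2% of variance.
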